# Effects of transcutaneous electrical nerve stimulation on pain, function, and descending inhibition in people with non-specific chronic low-back pain: a study protocol for a randomized crossover trial

**DOI:** 10.1186/s13063-024-08089-7

**Published:** 2024-04-06

**Keywords:** Low back pain, Transcutaneous electric nerve stimulation, Study protocol, Randomized controlled trial, Nociception, Pain measurement, Pain threshold, Analgesics

## Abstract

**Background:**

Low back pain (LBP) is a significant public health problem, is very prevalent, and is often characterized by the persistence of symptoms. Transcutaneous electrical nerve stimulation (TENS) may benefit people with chronic LBP because it can activate descending inhibitory pathways and inhibit central excitability. However, previous studies that have investigated the effects of TENS on pain in people with LBP have failed to use proper intensities of current, and the timing of the assessment of pain was not performed during the peak of the analgesic response or functional activities. Therefore, the present study aims to assess the effects of TENS on measures of pain, function, and descending inhibition using the maximal tolerable intensity of TENS in participants with LBP.

**Methods/design:**

This study will be a randomized crossover trial. The participants for this study will be recruited from various places, including the University of Hartford, physical therapy clinics, and local businesses in the Hartford area, as well as online websites geared towards clinical trial recruitment. A total of 34 participants will receive all three treatments: active TENS, placebo TENS, and no treatment control. The treatment order will be randomized using a website-based randomization tool. For active TENS, a modulating frequency of 2–125 Hz will be applied with a variable pulse duration and maximal tolerable intensity for 30 min. The TENS will be left on for post-treatment testing to assess the effects during its maximally effective period for a total of 50 to 60 min. Furthermore, the intensity may be turned down if muscle twitching is present to ensure blinding of the evaluator. For placebo TENS, the unit will deliver current for 45 s, ramping to 0 in the last 15 s. The primary outcome will be pain intensity at rest and with movement, determined using the numerical pain rating scale. The secondary outcomes will be pressure pain threshold, heat pain threshold, temporal summation of pain, conditioned pain modulation, sit-to-stand test, and repeated trunk flexion. The assessments will be performed immediately before and after treatment. Statistical analysis of the data obtained will consider a significance level of *p* < 0.05.

**Discussion:**

This study will provide evidence concerning the effects and mechanisms of TENS treatment in participants with chronic non-specific low back pain. The outcomes, including pain, function, and descending inhibition, will help us gain a greater understanding of how TENS can be used for these participants.

**Trial registration:**

ClinicalTrials.gov NCT05812885. Registered on 24th May 2023.

## Introduction

### Background and rationale {6a}

Low back pain (LBP) is a significant public health problem [1], is very prevalent [2–4], and is often characterized by the persistence of symptoms [2]. Unfortunately, substantial improvements in people with chronic LBP are rare, causing most people to live with the pain [2]. People with chronic LBP may have an exaggerated pain response to nociceptive input that may also cause symptoms distant from the site of the primary symptoms [5]. Historically, these symptoms were thought to be related to pathoanatomic changes to the muscles, ligaments, or joints. The severity of these structural changes weakly correlates with the clinical presentation and, in most cases, is not directly related to diagnostic image findings [6]. Individuals with chronic musculoskeletal pain generally show signs of central excitability. The central excitability may be directly correlated with the intensity and duration of pain [7]. Therefore, it is essential to reduce pain intensity and minimize the duration of pain to reduce central excitability [8].

Pain relief for individuals with chronic LBP should be aimed at treatments that reduce central excitability and increase central inhibition [8]. Research into chronic LBP treatment has demonstrated strong evidence that different types of exercise decrease pain and improve quality of life [9]. However, exercise itself may be painful, which may prevent a person from exercising. Thus, treatments aimed at decreasing pain should improve a person’s ability to exercise and participate in activities of daily living.

One treatment aimed at reducing central excitability and increasing central inhibition is transcutaneous electrical nerve stimulation [10, 11]. TENS is a “non-pharmacological” treatment for pain that is inexpensive, safe, and easy to use. Prior studies show that TENS utilizes opioid receptors both spinally and supraspinally to reduce sensitization of dorsal horn neurons, excitatory neurotransmitter release, and hyperalgesia [12]. Thus, TENS may be particularly useful in people with chronic LBP because it can activate descending inhibitory pathways (reduced in chronic low back pain patients) and inhibit central excitability (increased in chronic LBP patients).

Previous studies that have investigated the effects of TENS on pain in LBP patients have failed to use proper intensities of current, and the timing of the assessment of pain was not performed during the peak of the analgesic response or during functional activities [13]. Previous studies show that inadequate intensities do not reduce pain or increase pressure pain thresholds [12]. Further, TENS typically does not affect resting pain after abdominal surgery, while changes in pressure pain thresholds and pain with movement are reduced [10, 14, 15]. A recent randomized controlled trial addressed these limitations and showed a significant reduction in movement-evoked pain and fatigue with TENS in individuals with fibromyalgia [11]. However, it is unclear if the same reduction, when using adequate experimental design, will also reduce pain in individuals with low back pain. Thus, the current study proposes to assess the effects of TENS on measures of pain, function, and descending inhibition using the maximal tolerable intensity of TENS applied to a large area of the trunk in people with non-specific chronic low-back pain.

### Objectives {7}

This study aims to assess the effects of TENS on measures of pain, function, and descending inhibition in people with chronic non-specific LBP.

### Trial design {8}

The study will be a crossover design and will be conducted at the University of Hartford. The study protocol was approved by the Institutional Review Board (IRB) of the University of Hartford, it was registered online on ClinicalTrials.gov, and will be reported according to CONSORT guidelines [16]. The protocol was developed following the recommendations of SPIRIT (Standard Protocol Items: Recommendations for Interventional Trials). The RCT will have a blinded evaluator.

## Methods: participants, interventions, and outcomes

### Study setting {9}

The study will be carried out at the Department of Rehabilitation Sciences of the University of Hartford, West Hartford, CT, USA.

### Eligibility criteria {10}

To determine eligibility for participation in the study, potential candidates must fill out an online form. The form will collect information about their prior use of TENS, any changes in back and leg sensitivity, pregnancy status, history of chronic illness, presence of pacemaker, epilepsy, skin allergies, injuries or diseases, willingness to change pain medication within the next 3 weeks, peripheral neuropathies, and history of serious injury, illness, or surgery on their back or lower limbs. Once the screening form is completed, a research team member will contact the candidates via phone to ensure they meet all the inclusion and exclusion criteria.

#### Inclusion criteria

Individuals with non-specific LBPOn a stable medication regimen during the 4 weeks preceding the studyChronic LBP for at least 3 monthsNumerical pain rating scale (NPRS) score ≥  3 and ≤ 8 for pain intensityAge between 18 and 60 years [17, 18]Men and womenTENS naive or have not used TENS for 5 years

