#### Active TENS

An EMPI Select TENS unit will be used to deliver the active TENS intervention. A modulating frequency TENS (2–125 Hz) will be applied with a variable pulse duration, waveform of an asymmetrical biphasic square wave, and maximal tolerable intensity [11, 15]. With this specific unit, current intensity ranges from 0.5 to 60.0 mA and the participants will be educated prior to intervention on what they will feel. TENS will be placed for 30 min after baseline testing and then remain on for the post-assessment tests to assess the effects during its maximally effective period [10] for a total of 50 to 60 min. Every 5 min, the subject will be asked if the intensity can be increased, decreased or remain the same to maintain the same level of intensity. The intensity may be turned down if muscle twitching is present during post-assessment testing maintain blinding of the evaluator.

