#### Placebo TENS

An EMPI Select TENS unit will be used to deliver the placebo TENS intervention. The placebo TENS unit appears identical to that of the active TENS unit and will deliver current for 45 s, ramping to 0 in the last 15 s. This allows the person receiving the TENS to be blinded to the treatment applied.

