### Participant timeline {13}

Participants will be asked to complete a self-administered questionnaire that collects demographic information such as age, sex, marital status, education level, ethnicity, race, income, and history of surgeries. Weight will be measured using a calibrated electronic scale, height will be measured using a stadiometer, and the body mass index will be calculated. Participants will be randomized to treatment group order after providing written consent. The order of active TENS, placebo TENS and no TENS will be randomized via the website (randomization.com). Simple randomization results will be concealed in sealed opaque envelopes with consecutive numbers and will not be available to the outcomes assessor. The envelopes will be signed, dated, and opened by the TENS allocator before the TENS application and after the outcomes assessor has left the room.

An overview of the study procedures is shown in Fig. 1.

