## Assignment of interventions: allocation

### Sequence generation {16a}

The order of active TENS, placebo TENS and no TENS will be randomized via the website (randomization.com).

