## Assignment of interventions: blinding

### Who will be blinded {17a}

Both the evaluator and data analysts will be blinded to the randomization and intervention processes. The participants and the researcher responsible for the treatment cannot be blinded due to the nature of the interventions.

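### In half of the possible treatment orders the 45-second placebo follows maximal active TENS, and the analysis pools these placebo sessions with the others without a period or order term

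*Protocol article*

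**What the plan says.** Under Inclusion criteria, entrants must be TENS "naive or have not used TENS for 5 years". No reason is given for the rule.

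The Abstract sets the crossover: "A total of 34 participants will receive all three treatments: active TENS, placebo TENS, and no treatment control". The order is randomized through a website (Sequence generation {16a}), and Participant timeline {13} adds: "Simple randomization results will be concealed in sealed opaque envelopes with consecutive numbers". No order is excluded and no balance between orders is required.

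Active TENS runs at maximal tolerable intensity for 50 to 60 minutes in total, and the participant takes part in setting it: "Every 5 min, the subject will be asked if the intensity can be increased, decreased or remain the same". The placebo unit "will deliver current for 45 s, ramping to 0 in the last 15 s", and the Placebo TENS section concludes: "This allows the person receiving the TENS to be blinded to the treatment applied". Who will be blinded {17a} says the reverse: "The participants and the researcher responsible for the treatment cannot be blinded due to the nature of the interventions".

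The primary outcome is self-rated pain at rest and with movement. Statistical methods {20a} compares conditions by repeated measures ANOVA with Tukey, or by Friedman with pairwise Wilcoxon tests, and names no period or order term. Section {20b} says that no subgroup or adjusted analyses are planned at present. The blinding check questions only the outcomes assessor.

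**The concern.** A placebo that delivers current for 45 seconds may pass as real to someone who does not know what real treatment feels like. It is much less likely to do so once that person has had up to an hour of active TENS, with the intensity discussed every five minutes. Whatever protection limited prior exposure gives the placebo lasts only until the active session, and the randomized order decides whether that session comes first.

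The outcome is the participant's own pain rating, so expectation can act on it directly. If the placebo response is weaker after active TENS, the pooled active-minus-placebo difference mixes a treatment effect with an unmasking effect, and the planned analysis cannot show how much is which. The trial's hypothesis (Discussion) rests on active TENS doing better than placebo as well as no treatment, so this contrast matters.

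**Working it through.** **Inputs from the protocol.** N = 34, SD 1.9, target difference 2 points, 80% power, 5% alpha, 15% loss (Sample size {14}); three conditions, simple randomization, no restriction on order ({13}, {16a}); Tukey after repeated measures ANOVA ({20a}).

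**Assumptions not in the protocol.** All six orders are equally likely; tests are two-sided; the within-person correlation ρ lies between 0 and 0.7; pain in a placebo session after active TENS is b points worse, with b = 0.5, 1 or 2.

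**1. The plan's own figure.** 4 × (1.9 × 2.8016 / 2)² = 28.33, where 2.8016 = 1.9600 + 0.8416. Then 28.33 / 0.85 = 33.3, rounded up to 34. The stated N reproduces, and this point does not affect it. Completers: 34 × 0.85 = 28.9, taken as 29.

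**2. Orders (A active, P placebo, N no treatment).**
- Placebo after active: A-P-N, A-N-P, N-A-P.
- Placebo before active: P-A-N, P-N-A, N-P-A.

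That is 3 of 6. Expected number with placebo after active: 34 × 0.5 = 17; the binomial(34, 0.5) 95% range is 11 to 23. Among 29 completers the expectation is 14.5.

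**3. Shift of the pooled contrast.** Shift = b × share of post-active placebo sessions, about b/2. For b = 1 it is 0.5 on average, and 11/34 = 0.32 to 23/34 = 0.68 over the range in step 2.

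**4. Spread of the paired difference.** If half of the participants lose b points, the mixture adds b²/4 to the variance: Var = 2 × 1.9² × (1 − ρ) + b²/4. Example for ρ = 0, b = 2: 7.22 + 1 = 8.22, SD 2.87, against 2.69 without the mixture term.

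**5. Rejection with no true effect.** Simulation with 29 completers, three conditions, no true difference between conditions, and the Tukey comparison of active with placebo. The Tukey critical value for three means and 56 degrees of freedom is 3.405, which is 3.405/√2 = 2.41 on the t scale. With b = 0 this single comparison rejects in about 2% of trials.

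| b (assumed) | shift | ρ = 0 | ρ = 0.5 | ρ = 0.7 |
|---|---|---|---|---|
| 0.5 | 0.25 | 3% | 5% | 7% |
| 1 | 0.5 | 9% | 16% | 27% |
| 2 | 1.0 | 33% | 57% | 77% |

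These figures are good to about one percentage point and apply to the ANOVA route only.

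**6. Cost of splitting by order.** The standard error ratio is √(34/17) = 1.41. At ρ = 0 it is 2.69/√34 = 0.46 against 2.69/√17 = 0.65. With 14 completers, power for a 2-point difference is 73% at ρ = 0 and 95% at ρ = 0.5.

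**The case against.** The strongest reply has four parts.

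- **The entry rule is not breached.** A reader might infer that the rule exists to keep the placebo credible and that the trial then violates it. The protocol does not support this. It gives no reason for the rule, admits people who used TENS more than five years ago, and applies the rule at entry only. Receiving trial treatment breaks nothing. This part stands.
- **Sham-controlled crossovers generally have this feature, and model terms belong in the analysis plan.** The first half is fair. On the second, the point is not silence: {20a} names tests that compare conditions across all orders, and {20b} says no adjusted analysis is planned at present. An analysis plan that is not shown may still add a period term.
- **Size and direction are unknown.** This stands. No figure in the protocol shows that b is above zero, and b = 2 equals the whole target difference. A reader might infer that the TENS effect will be overstated. That does not follow, because relief carried over from active TENS would lower pain in later placebo sessions and bias the contrast the other way. A reader who uses an unadjusted paired test and leaves out the mixture variance would get 16-42% for b = 1 and 49-94% for b = 2. The plan's Tukey test does not support rates that high.
- **Placebo-before-active sessions are not known to be masked.** This also stands. {17a} denies participant blinding altogether, and participants are not asked to guess their treatment, so nothing in the protocol separates credible from non-credible sessions.

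**Conclusion.** The structural point holds. Half of the possible orders place the placebo where its masking is weakest, the outcome is self-rated, and the stated analysis averages over order. The shift in the active-placebo contrast is about b/2 for an assumed b. A loss of 0.5 point leaves the false-positive rate between about 3% and 7%. A loss of 1 or 2 points raises it clearly, but those sizes are illustrative. The results also assume equally likely orders, 29 completers and a correlation between 0 and 0.7.

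The protocol supports neither a prediction that the result will be biased in favour of TENS nor a division of placebo sessions into valid and invalid ones. It does support saying that a foreseeable dependence on order would go unexamined although the data to examine it will be collected, and that the Placebo TENS section and {17a} contradict each other on participant blinding.

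**What to change.** 1. Reconcile the Placebo TENS section with {17a}, so that the protocol makes one statement about participant blinding.
2. Analyse pain with a within-person model that includes period as well as condition.
3. Pre-specify, as a sensitivity analysis, the active-minus-placebo estimate separately for placebo-before-active and placebo-after-active orders. Report both with confidence intervals.
4. State in advance that a difference between the two may reflect unmasking or carryover, and that the split cannot tell them apart.
5. Describe the placebo-controlled result as robust only if the placebo-before-active estimate is consistent with the pooled one. The pooled estimate stays the main result, because making the claim depend on half of the sample would give up too much precision.

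The cost is a period term, one sensitivity analysis and a few sentences. No extra participants, visits or measurements are needed. The downside is precision: each order-specific estimate rests on about 14-15 completers, with a standard error about 1.4 times larger, so a modest difference between the two could be missed.

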#### Exclusion criteria

Serious spinal disorders, such as fractures, tumors, or inflammatory arthritis disease; nerve root disorders confirmed by neurological testsNeurological or rheumatological diseasesFibromyalgia or other chronic pain conditionSevere cardiorespiratory diseasePregnancyEpilepsySkin infection, lesions, or change in sensation at the TENS application siteCancerCardiac pacemaker, defibrillator or implanted stimulatorSkin allergy to electrodesUse of opioidsIndividuals who have ingested any sedative, anti-inflammatory or analgesic medications, and alcoholic substance in the last 48 h before the intervention.

### Who will take informed consent? {26a}

Data collection will only start after the participants have signed an informed consent form, which the evaluator will explain.

### Additional consent provisions for collection and use of participant data and biological specimens {26b}

N/A. No biological specimens will be collected as part of this trial.

## Interventions

### Explanation for the choice of comparators {6b}

Previous studies regarding TENS application in participants with chronic LBP have failed to measure pain during the peak of the analgesic effect or have not used adequate current intensities. Therefore, the proposed research will assess the effects of TENS immediately after the intervention and use the maximal tolerable intensity.

### Intervention description {11a}

#### Electrode placement

Four 5  ×  5-cm electrodes (ValuTrode®; Axelgaard, Fallbrook, CA) will be placed over the lumbar paraspinal muscles, immediately above and below the spinal level corresponding to pain complaint, for treatment [13, 19]. These self-adhesive electrodes are commercially available and will be purchased for each subject.

#### Active TENS

An EMPI Select TENS unit will be used to deliver the active TENS intervention. A modulating frequency TENS (2–125 Hz) will be applied with a variable pulse duration, waveform of an asymmetrical biphasic square wave, and maximal tolerable intensity [11, 15]. With this specific unit, current intensity ranges from 0.5 to 60.0 mA and the participants will be educated prior to intervention on what they will feel. TENS will be placed for 30 min after baseline testing and then remain on for the post-assessment tests to assess the effects during its maximally effective period [10] for a total of 50 to 60 min. Every 5 min, the subject will be asked if the intensity can be increased, decreased or remain the same to maintain the same level of intensity. The intensity may be turned down if muscle twitching is present during post-assessment testing maintain blinding of the evaluator.

#### Placebo TENS

An EMPI Select TENS unit will be used to deliver the placebo TENS intervention. The placebo TENS unit appears identical to that of the active TENS unit and will deliver current for 45 s, ramping to 0 in the last 15 s. This allows the person receiving the TENS to be blinded to the treatment applied.

#### No treatment control

Participants will receive no TENS treatment but will perform a quiet rest period of 30 min instead of TENS. All other procedures will be the same. Therefore, this group will control for the placebo effect and repeated testing.

### Criteria for discontinuing or modifying allocated interventions {11b}

There will be no changes in the treatment allocation order. If participants discontinue treatment, recent data will be computed for the analyses according to the intention-to-treat principle, and the reason for the withdrawal from the study will be recorded.

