### Sample size {14}

Sample size was calculated to determine the total number of study participants needed to detect a difference of 2 points for the pain intensity outcome, which is considered a clinically relevant value for LBP [32], as measured using the NPRS, with a standard deviation of 1.9 points [13]. An 80% statistical power, 5% alpha, and a possible sample loss of 15% were considered. Thus, a total of 34 participants will be needed. This calculation was performed using Minitab v.17 software (State College, PA, USA).

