### Plans to promote participant retention and complete follow-up {18b}

The researchers will be in weekly contact with the study participants. Twenty-four hours before treatment sessions, a researcher will send text messages to remind participants of the treatment date and time. This procedure will ensure that participants receive the necessary attention and will assist in fully accompanying them during the research. If any participant fails to attend the appointment, the researchers will immediately call to inquire about the reasons for the no-show. If participants abandon the trial, the reasons will be recorded, the most recent data will be compiled, and analysis will be performed using the intention-to-treat principle.

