### Methods in analysis to handle protocol non-adherence and any statistical methods to handle missing data {20c}

The intention-to-treat analysis will be used, and the missing data will be handled appropriately following established guidelines [35].

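### Using the most recent data of participants who leave, if read as carry-forward, would copy scores between treatments in this crossover and shrink the active-placebo estimate

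*Protocol article*

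**What the plan says.** The design is a three-treatment crossover: "A total of 34 participants will receive all three treatments: active TENS, placebo TENS, and no treatment control" (abstract, Methods/design). Outcomes {12} places one assessment before and one after treatment, with no later follow-up.

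Four sections of the protocol article deal with participants who leave:

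- Criteria for discontinuing {11b}: "If participants discontinue treatment, recent data will be computed for the analyses according to the intention-to-treat principle".
- Retention {18b}, on abandonment: "the most recent data will be compiled, and analysis will be performed using the intention-to-treat principle".
- Adherence {11c} covers the same event but mentions only an intention-to-treat analysis.
- Missing data {20c}: "the missing data will be handled appropriately following established guidelines". It cites a reference and names no method.

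Statistical methods {20a} prescribes repeated measures ANOVA with the Tukey test, or the Friedman test followed by Wilcoxon signed-rank comparisons. ANOVA in its usual form and Friedman both need a value under every treatment for each person.

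**The concern.** Under {11b} and {18b} the latest data of someone who has left go into an analysis that requires three scores per person. Either the empty cells are filled with the latest score or the person is dropped, and dropping does not fit the wording. Carry-forward is therefore the natural reading.

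In a parallel-group trial, a carried value at least belongs to the assigned treatment. Here a missed session has no earlier post-treatment value of its own, so the carried score comes from a session under another treatment. The within-person contrast, which is what a crossover estimates, is then partly or wholly removed for that person. The estimate, its confidence interval and the planned Cohen's d for the primary NPRS outcome are at stake, because readers will compare them with the protocol's 2-point clinically relevant difference.

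**Working it through.** **Inputs from Sample size {14}.** The trial is to "detect a difference of 2 points for the pain intensity outcome", "with a standard deviation of 1.9 points". "An 80% statistical power, 5% alpha, and a possible sample loss of 15% were considered". "Thus, a total of 34 participants will be needed".

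**Reproducing the plan's figure.** A two-group normal approximation with a two-sided 5% level gives n per group = 2 × 1.9² × (1.960 + 0.842)² / 2² = 14.17. The total is 28.33, and 28.33 / 0.85 = 33.3, rounded up to 34. The figure is reproduced. A 15% loss of 34 is about 5 people, leaving 29.

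**Leaving after session 1.** One score serves for all three treatments, so every contrast for that person is 0. The expected estimate is 2.0 × 29/34 = 1.71, or 2.0 × 0.85 = 1.70 with exactly 15%.

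**Leaving after session 2.** The session 2 score is copied into session 3. With A active, P placebo and N no treatment, the active-placebo contrast becomes:

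| Order | Contrast after filling |
|---|---|
| A-P-N | A − P |
| P-A-N | A − P |
| A-N-P | A − N |
| P-N-A | N − P |
| N-A-P | 0 |
| N-P-A | 0 |

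The average is 1/3(A − P) + 1/6(A − N) + 1/6(N − P) = 1/2(A − P). This does not require placebo to equal no treatment. The expected estimate is 2.0 × (1 − 0.15/2) = 1.85.

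**Other loss rates (assumed).** A 5% loss gives 1.90 to 1.95, and a 25% loss gives 1.50 to 1.75.

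**Precision and coverage.** I simulated 6,000 trials per row with these settings: one score per session, N = 34, SD 1.9, 5 withdrawals unrelated to outcome, orders drawn at random, active 2 points better, and placebo equal to no treatment. Within-person correlation is not given in the protocol, so it was varied from 0 to 0.8. Repeated measures ANOVA after carry-forward was compared with the same analysis of the 29 completers.

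| Correlation | Leave after session | Estimate, carry-forward | SE, carry-forward | SE, completers | SE lower by | Coverage, carry-forward | Coverage, completers |
|---|---|---|---|---|---|---|---|
| 0 | 1 | 1.71 | 0.435 | 0.496 | 12% | 89.7% | 94.5% |
| 0 | 2 | 1.86 | 0.455 | 0.496 | 8% | 93.8% | 94.9% |
| 0.5 | 1 | 1.71 | 0.315 | 0.350 | 10% | 85.6% | 95.1% |
| 0.5 | 2 | 1.85 | 0.329 | 0.352 | 7% | 93.3% | 95.1% |
| 0.8 | 1 | 1.70 | 0.214 | 0.222 | 4% | 74.4% | 94.9% |
| 0.8 | 2 | 1.85 | 0.218 | 0.222 | 2% | 90.7% | 94.8% |

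Completers return 2.00 in every setting, to within 0.01. Error degrees of freedom are 2 × 33 = 66 after filling, against 2 × 28 = 56 for completers.

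**Tests.** With no true effect and correlation 0.5, carry-forward rejects in 5.1% to 5.4% of trials. For a 1-point effect, power is 80.7% after filling and 80.1% with completers. At 2 points it is at least 97% either way. The reason is simple: if all leave after session 1, the filled estimate is the completers' estimate times 29/34, so its sampling spread shrinks by the same factor. The coverage loss therefore comes from the shifted centre. At correlation 0.5 with all leaving after session 1, the reported SE (0.315) is slightly above the estimate's actual spread (0.302).

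**The case against.** The strongest reply is that the protocol never says a value is carried forward or imputed. Compiling recent data could mean collecting and analysing whatever was observed before withdrawal, and on that reading no bias arises. The section devoted to missing data leaves the method to cited guidelines. If someone leaves during a session, the latest value may be that session's own pre-treatment score, which is not copying between treatments, although it also pulls the change towards zero. All of this stands, and it makes carry-forward an inference. It does not remove the point: the wording appears twice, {20c} does not withdraw it, and the tests in {20a} press towards filling the cells.

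Several stronger readings are tempting but not supported:

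- That {20c} contradicts {11b} and {18b}. Since {20c} names no method, one can say only that the sections need to be aligned.
- That every contrast in this trial will be biased towards zero. The shrinkage is an average over balanced orders with non-informative withdrawal. Simple randomization (Participant timeline {13}) does not guarantee balance, and withdrawals clustered in certain orders could exaggerate a single contrast.
- That half the orders give an exact zero after a session 2 withdrawal. Two of the six do. A third (P-N-A) has expectation zero only if placebo equals no treatment.
- That the rule would create false positives or cost material power. The simulation shows neither.

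The size is also modest: the 15% is a planning allowance, and the largest shrinkage needs every withdrawal to follow session 1.

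**Conclusion.** The point holds as a should-fix matter. Read in the natural way, the rule places one treatment's score in another treatment's session. At the planned 15% loss it would shrink a true 2-point active-placebo difference by about 0.15 to 0.30 points on average, to 1.70 to 1.85. The SE would be about 2% to 12% below that of completers, and coverage of the true difference would fall from about 95% to between 74% and 94%. The harm is to the estimate and its interval; type I error and power are practically unaffected.

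This rests on carry-forward being what the wording intends, on orders balanced on average, on withdrawal unrelated to outcome, and, for the SE and coverage, on an assumed within-person correlation of 0 to 0.8 with SD 1.9 per session. The planned sample size is not called into question by this point.

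**What to change.** - In {11b} and {18b}, replace the rule on recent data with a statement that every session actually observed is analysed and no value is carried from one session to another.
- Align {20c} with that statement.
- Amend {20a} so that the primary NPRS analysis is a linear mixed model on all observed sessions, with participant as a random effect and treatment and period as fixed effects. Add a sensitivity analysis in participants who completed all three sessions. Any Friedman or Wilcoxon analysis should use observed data only.

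The cost is small but goes beyond wording, because the primary model in {20a} changes. The report would also show fewer than 34 complete participants if some leave, and the SE would be slightly larger. The mixed model can be fitted in the SPSS version already named, and neither recruitment nor trial conduct is affected. The change should be made before the data are analysed.
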